#### Study data

Our primary analyses will address the progression criteria as presented above and will be largely descriptive in nature. We will develop a formal Statistical Analysis Plan (SAP) to outline all planned analyses, including conventions on the treatment of missing data, principles of selection of explanatory factors and covariates in statistical models, and the reporting of raw and adjusted outcomes.

We will produce a CONsolidated Standards Of Reporting Trials (CONSORT) flowchart for patient recruitment appropriate for cluster trials [32]. Study data will be summarised by intervention or control arm, and we will further summarise key demographic and outcome variables by study site. Although this feasibility study is not intended to provide a definitive evaluation of the THN intervention, we will assess and report differences in outcomes via appropriate generalised mixed linear models, adjusting for key covariates and factors.

For the follow-up population (B), we will also summarise linkage rates and characteristics for those not linked versus those linked, coding completion rates for ED and ambulance service events, and carry out a comparison of data obtained from routine sources. We will report these data by site and in total. We will provide details on data completeness related to the criteria for determining progression to a full trial.

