## Methods

### Setting, recruitment, and consent

We will carry out a feasibility study in the emergency care environment, involving study sites defined geographically as an ED and its catchment area within the local emergency ambulance service. For example, one study site comprises the ED at Bristol Royal Infirmary, a large city centre hospital in England, and its catchment area, the surrounding urban area from which the South West Ambulance Service Foundation Trust routinely conveys patients to this ED. The study will be delivered in the form of an RCT clustered by study site, using retrospective anonymised linked routine data to capture patient outcomes. We will also collect qualitative data to gain an understanding of the processes of implementation of the intervention and experiences of service users and providers. Finally, we will collect data related to patient safety.

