**Fig. 1 Fig1:**
[figure not shown]
Overall CONSORT diagram

At each intervention site, with approximately 2000 people thought to be at high risk of fatal overdose, we expect 200 to make contact with the ED or ambulance service over the course of 1 year and be eligible to receive THN. We expect 100 contacts via the ED, and another 100 contacts via the corresponding ambulance service.

We will use routine linked data to identify the population to be included at each site in outcome analyses via a predictive model to be fully specified within our study. The model will include opioid users who have made contact with included services over a period of 24 months previous to our recruitment phase. Individuals predicted to be at risk of death from opioid overdose will include those attending ED or being attended by a 999 paramedic during the recruitment phase and their peers. We expect the follow-up population to be at least 1520 people across four sites.

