#### Randomisation

We approached all UK ambulance services and received five positive responses from potential sites with matched EDs, who were able to demonstrate the capacity and resources to participate. Of these potential sites, four demonstrated sufficient geographic separation from other study sites to mitigate potential cross-contamination of study populations. From these four sites, we selected two to be intervention sites and two to be control sites; a member of the research team (MJ) picked one set of study site allocations at random from the set of all possible allocations, each contained within separate sealed opaque envelopes.

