### Outcomes

We will measure outcomes related to the feasibility of the study in terms of the intervention and methodology, including whether we can capture sufficient data to measure clinical outcomes and health economics.

Outcomes related to the feasibility of the study include sign up of sites; proportion of eligible staff recruited and trained to deliver the intervention; proportion of eligible participants identified, number of kits issued; and the adverse event rate in intervention and control sites.

We will also assess the feasibility of collecting clinical outcomes from anonymised linked routine health records over a period of 12 months, acknowledging that feasibility will also depend on the quality and availability of routine data.

The proposed primary outcome is mortality (all deaths and those known to be opioid-related). Secondary outcomes include intensive treatment unit (ITU) admissions, ED visits, and in-patient admissions (all visits/attendances as well as those known to be opioid-related), further 999 calls as well as THN kits issued and costs. Our feasibility study will not be adequately powered to detect statistically significant differences in these proposed outcomes between intervention and control arms.

We will assess the feasibility of using routine data sources to estimate health care costs. Total NHS costs for each patient will be calculated based on the staff training costs, patient training costs, and other NHS costs (e.g. those for 999 calls, ED attendances, and admissions). Training costs will be calculated using records of completion of training, staff recall of patient training, and then combined with NHS salary data. Other NHS costs will be based on routine data for the relevant ED and ambulance service trusts.

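### With two randomised sites per arm, arm differences from generalised mixed models rest on 2 degrees of freedom, and default large-sample intervals can be far too narrow for the commoner outcomes

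*Protocol article*

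**What the plan says.** The unit of randomisation is the study site, an ED with its ambulance catchment area: "The study will be delivered in the form of an RCT clustered by study site" (Setting, recruitment, and consent). The Randomisation section fixes the number: "From these four sites, we selected two to be intervention sites and two to be control sites". A team member "picked one set of study site allocations at random from the set of all possible allocations".

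For the comparison of arms, the Study data part of Data analysis says that "we will assess and report differences in outcomes via appropriate generalised mixed linear models, adjusting for key covariates and factors". It gives no random-effects structure, degrees-of-freedom method or form of interval, and it refers further detail to a SAP. The same section says that the primary analyses address the progression criteria and are mainly descriptive, and that key outcomes will also be summarised by site.

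On size, the Sample size section says "We expect the follow-up population to be at least 1520 people across four sites". On power, the Outcomes section says "Our feasibility study will not be adequately powered to detect statistically significant differences".

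**The concern.** The article names a model class for the arm comparison, and the standard inference for that class relies on having many clusters. Here there are four. The between-site variance must be estimated from two sites within each arm, and it will often be estimated at or near zero. When that happens, the patients are treated almost as if they were independent. Even when the variance is not lost, a normal critical value is wrong for an effect with 2 df.

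Saying that the study is underpowered does not deal with this. Low power means that intervals are honestly wide. The risk here is that they are too narrow, so that an ordinary difference between sites looks like an effect of the kits. That matters because the Safety monitoring section reads service use and death as markers of adverse behavioural change, and because the Data Monitoring Committee will see comparative data. The article does not say that mixed models will be used for either purpose, but a modelled difference with a short interval would naturally be read in that light.

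**Working it through.** **Inputs from the article.** Four sites, two per arm (Randomisation). Follow-up population of at least 1520 (Sample size), so 1520 / 4 = 380 per site on average. The article gives no alpha, ICC, event rate or interval width for the arm comparison, so it has no figure of its own to reproduce.

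**Assumed inputs.** Event rates of 2%, 10% and 30%; ICC from 0 to 0.05 on the latent (log-odds) scale; equal sites of 380; no true effect.

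**Step 1, degrees of freedom.** Sites minus arms = 4 - 2 = 2. The 97.5% point of t on 2 df is 4.303, against 1.960 for the normal. The ratio is 4.303 / 1.960 = 2.20, so for the same standard error the interval should be 2.2 times as wide. If the standard error is a proper 2-df estimate, a multiplier of 1.96 gives 81% coverage.

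**Step 2, randomisation distribution.** There are C(4,2) = 6 possible allocations. An exact two-sided test cannot give a p-value below 2/6 = 0.33.

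**Step 3, coverage.** Random-intercept logistic models were fitted by maximum likelihood, with 500 simulated trials per setting. The latent site variance is ICC × (π²/3) / (1 - ICC). The table gives coverage of the nominal 95% Wald (z) interval:

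| Event rate | ICC 0 | 0.005 | 0.01 | 0.02 | 0.05 |
|---|---|---|---|---|---|
| 2% | 96% | 96% | 94% | 91% | 83% |
| 10% | 96% | 88% | 83% | 81% | 71% |
| 30% | 96% | 82% | 78% | 73% | 61% |

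The simulation error is √(0.95 × 0.05 / 500) ≈ 1 percentage point near 95%, and about 2 points at the lower values. The site variance was estimated at about zero in 14% to 87% of fits, depending on the setting.

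**Step 4, why the event rate matters.** At ICC 0.01 the latent site variance is 0.01 × 3.290 / 0.99 = 0.033. The binomial variance of one site's log-odds is 1 / (380 × p × (1 - p)): 0.134 at 2%, 0.029 at 10% and 0.0125 at 30%. Site variation is therefore about a quarter of the sampling noise at 2%, about equal to it at 10%, and 2.7 times as large at 30%. With a rare outcome, sampling noise hides the site effect, so ignoring that effect costs little.

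**Step 5, alternatives.**
- Site-level t intervals on 2 df covered 93% to 97% in every setting.
- Mixed-model intervals with a t(2) multiplier covered 94% to 100%, except 87% at a 30% event rate and ICC 0.05.
- At a 10% event rate and ICC 0.02, the median width on the log-odds scale was 0.74 for the z interval and 2.24 for the site-level t interval, a ratio of 2.24 / 0.74 = 3.0.

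**The case against.** The strongest reply is that the article has not committed the error. The sentence promises no interval, test or p-value. It calls the models appropriate, and a SAP that is not shown may set a 2-df or small-sample method. A mixed model with a t(2) reference would satisfy the wording and performed acceptably in all but one setting. This stands in part: the narrowness comes from z-based inference, which the article neither states nor excludes. It does not remove the point, because the model class is already fixed, its standard inference fails with four clusters, and the simpler site-level method held its coverage throughout.

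The article also plans site summaries, disclaims power and says that the comparison is not definitive. That limits the harm, but it does not correct an interval that is too short.

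A reader might infer three stronger things that the document does not support:
- *Every outcome will have intervals that are far too narrow.* At an assumed 2% event rate and ICC up to 0.01, z coverage was 94% to 96%. If the proposed primary outcome, mortality, is that rare, it may be little affected. Costs were not examined.
- *The modelled effects drive the decision to proceed.* None of the progression criteria uses a modelled effect or interval. The only between-arm criterion is a threshold on the difference in serious adverse event rates, and no model is named for it.
- *Site-level covariates will use up a further degree of freedom.* One would leave 1 df, but the article names none.

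**Conclusion.** The point holds conditionally. Two sites per arm give 2 between-site degrees of freedom and a site variance that cannot be estimated reliably; this follows from the design. If default z inference is attached to the planned models, 95% intervals would cover about 61% to 88% at event rates of 10% and 30% with ICC 0.005 to 0.05. At a 2% event rate, coverage is near nominal up to ICC 0.01 and falls to 91% at 0.02 and 83% at 0.05. The ICCs, the event rates and the equal site sizes are assumptions. The document does not show that such intervals will be reported, and the feasibility conclusions do not rest on them. The wording is still worth changing, because it directs the comparison to a method that needs more clusters than the trial has.

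**What to change.** In the Study data section, or in the SAP under it:
- Make the four site-level rates for each outcome, risk-adjusted within site where useful, the main presentation. This builds on the site summaries already planned.
- Report any arm difference with a site-level t interval on 2 df (critical value 4.30), or with no interval.
- Give no p-values for arm differences.
- Keep patient-level models for risk adjustment and for event rates used in planning.

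Comparing each site with its own 24 months before recruitment is not a substitute. The Sample size section uses service contact in that period to select the follow-up population. People followed up must have survived it, so baseline mortality would be zero by construction, and selection on contact would inflate baseline service use.

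The cost is a change of wording, a simpler analysis and wider stated intervals: by a factor of 2.2 from the critical value alone, and about 3 at a 10% event rate with ICC 0.02.

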#### Qualitative data

We will use NVIVO to manage the qualitative data and carry out a thematic analysis of interview transcripts. Transcripts will be imported into NVIVO and be read and re-read to ensure familiarity with the data before coding. One researcher will develop and refine initial codes, with coding undertaken both with reference to NPT as a theory for evaluating the potential for normalisation of the intervention as a change of working practices in emergency settings [33] and ‘grounded’ in the data. Codes will be reviewed and emerging concepts used to develop themes. A second researcher will independently code a subsample of transcripts for comparison and discussion before further refinement of the coding structure and themes by the first researcher. Patient and public involvement (PPI) members will be involved in the qualitative analysis by co-developing themes and reviewing drafts of findings. Data from service providers at intervention sites will be compared within sites across time and also between sites for commonalities and divergence in themes.

### Trial management

A Trial Management Group (TMG) will manage the project and report to the independent Trial Steering Committee (TSC) at appropriate intervals. The Chief Investigator will chair the TMG which will meet every 3 months. The TMG will comprise all co-applicants, named collaborators, PPI members, and researchers.

The TSC will oversee the conduct and progress of the trial and adherence to the protocol, patient safety, and the consideration of new information of relevance to the trial. Two PPI members are full members of the TSC.

A Data Monitoring Committee (DMC) will monitor study data at interim periods and make recommendations to the TSC on whether there are any ethical or safety reasons why the trial should not continue. Its members will have access to comparative data and interim analyses and may request the un-blinding of such data at any time. The DMC will also consider requests for the release of data. The DMC may be asked by the TSC, Trial Sponsor, or Study Funder to consider data emerging from other related studies. If new evidence becomes available during the course of the trial, it is the responsibility of the trial and/or Data Manager to provide that information to the DMC to allow them to consider such issues and make recommendations on the continuation of the trial to the TSC.

Any risks identified throughout the trial will be documented in a risk log and monitored. This will be reported to the TMG and escalated to the TSC if appropriate.

### Public and patient involvement

We have involved public and patient members throughout this study to strengthen research rigour [34]. PPI members have experience of opioid addiction through family and voluntary networks. They have contributed to developing this study using personal experience to highlight the relevance of the research questions and comment on data collection methods and selection of outcomes. We also discussed the project with drug service users and voluntary sector service providers in the community. PPI members were named as co-applicants on the funding proposal. They will remain involved as members of the Trial Management Group and relevant subgroups. They will contribute to study management, reporting and dissemination through papers. Additionally, we have recruited two more individuals with relevant experience to be involved in the Trial Steering Committee. We will support all public and patient members to collaborate as equal members throughout the study [35].

#### Dissemination

In addition to publishing results in scientific journals, we will engage with third sector organisations, and media and communication departments at participating institutions, and we will disseminate findings and raise awareness about the trial and wider issues related to implementation. We will develop a proposal for funding for a fully powered trial, should this be supported by our findings.

## D**iscussion**

This study is the first to our knowledge to use routine anonymised linked data to identify the target population and measure outcomes related to a peer administered anti-overdose intervention such as THN in emergency settings. Our novel approach to capturing outcome data comes from the public health nature of the intervention, which is administered by laypeople to their peers who may or may not be the original recipient of the THN kit, as well as our own previous research indicating that individuals within the target population for the intervention move around a lot and are very difficult to follow-up using traditional methods.

The strength of this study lies in its novel approach establishing evidence in a new setting for an intervention which is already being distributed, albeit patchily, in response to opioid overdose as a growing public health concern. The study is being carried out by a team well placed to apply expertise and prior experience in the use of routine data in RCTs to contribute to the evidence base for THN in emergency settings, which is in urgent need of strengthening.

## Data Availability

Not applicable

## Abbreviations

ACMD: Advisory Council of the Misuse of Drugs
CONSORT: CONsolidated Standards Of Reporting Trials
DMC: Data Monitoring Committee
ECDS: Emergency Care Data Set
ED: Emergency
ITU: Intensive treatment unit
NHS: National Health Service
NPT: Normalisation process theory
NWIS: NHS Wales Informatics Service
PGD: Patient Group Direction
PPI: Patient and public involvement
PRIME: Primary and Emergency (including unscheduled) Care Research
RCT: Randomised controlled trial
SAIL: Secure Anonymised Information Linkage
SAP: Statistical Analysis Plan
THN: Take-home naloxone
TIDieR: Template for Intervention Description and Replication
TIME: Take-home naloxone in multicentre emergency setting
TMG: A Trial Management Group
TSC: Trial Steering Committee
VAT: Value-added tax
WHO: World Health Organization
